### Intervention: the JenMe program

A 12 week evidence-based lifestyle intervention program was developed by the team of Accredited Practising Dietitians at Jenny Craig Australia and was reviewed for content by paediatric psychologists specialising in behaviour change. The program will be delivered face to face to clients in the Jenny Craig Centres by consultants on a weekly basis for the duration of the program. Consultants in the centres have been trained by Jenny Craig and are not otherwise required to be trained health professionals. Specialised program materials will be used with participants and their parents or guardians. The participants will present to the centre to meet with a consultant weekly for 13 consecutive weeks (Weeks 0 to 12). Each week, a new element of the program (Table 1) will be delivered at each consultation to the adolescent, who will be encouraged to modify small behaviours each week. The order of topic deliverance will be directed by the adolescent and tailored to their needs. The parent or guardian will be involved in part of the consultation to ensure participation in the goal setting process. The program also encompasses a dietary plan that has been modelled on the dietary guidelines as outlined by the National Health and Medical Research Council’s (NHMRC, 2013) Australian Dietary Guidelines [22].

**Table 1 Tab1:** Topics covered over 12 weeks within the JenMe program

Eat Well		Move more	Live life
▪ Decoding drinks		▪ How to move more by tracking how you move less	▪ Body image
▪ Eating out for success		▪ Overcoming your activity barriers	▪ Learning from lapses
▪ Jenny at school & friends’		▪ Setting SMART goals	▪ Rewards & buddies
▪ Meals with the family and fast & healthy after school snacks		▪ Time for a physical activity challenge!	▪ Saying No
▪ Non-hungry eating & learning to eat with awareness			
**Independent menu planning**			
Getting started on your own	1. Your own menu guide	2. Working out grocery serves of recipes	3. Working out grocery serves of packaged foods from labels

Initially the participant will follow the menu that includes pre-packaged food provided by the commercial program, combined with their own grocery items. Throughout the program the adolescent, with the support of their consultant and parent or guardian will learn how to plan their own menus using all of their own foods, and either during or following the 12 week program, they will eventually transition onto their own menu planning (Table 1). In accordance with usual practice at Jenny Craig, once the 12 week ‘JenMe’ program is complete, adolescents have the option to receive ongoing, individually-tailored support, depending on the need for further weight-loss or weight-maintenance up to the age of 18 years of age as part of their Jenny Craig membership. Also, as with any commercial program, participants are free to withdraw from the program at any stage, for any reason.

### Wait-listed control

The wait-listed control group will receive standard healthy eating guidelines, the ‘Healthy Eating for Children’ booklet developed by the National Health and Medical Research Council based on the Australian Dietary Guidelines [22], and advised to maintain their current lifestyle habits for the control period. Wait-listed control participants will be offered the commercial weight management program at the end of the control period (12 weeks).

All study participants, from both the intervention and control groups will receive a free adolescent membership with Jenny Craig, which is valid until they are 18 years of age as well as a discount on all Jenny Craig food provisions for 12 months.

### Outcomes

#### Anthropometry

All participants will have their baseline weight, height, waist, and body composition (using bioelectric impedance analysis (BIA); BODYSTAT Quad Scan 4000, BODYSTAT Ltd., Douglas, Isle of Man, UK) measured by trained Jenny Craig consulting staff using standard operating procedures. BMI Z-score will be calculated by the lambda-mu-sigma (LMS) method using Centre for Disease Control reference data (http://www.cdc.gov/growthcharts/percentile_data_files.htm) which takes into account age and gender. Participants will be required to self-assess their pubertal status using the Tanner stages of puberty scale [23, 24]. The intervention group will have weekly weight measurements, height measured every 4 weeks and waist and body composition assessed by BIA measured at 0 and 12 weeks. Wait-listed control participants will have all measurements taken at 0 and 12 weeks only.

#### Dietary analysis

Intervention and wait-listed control participants will be required to complete a 4-day food diary, both in the week prior to commencement of the intervention or wait-listed period and again at 12 weeks. Dietary analysis of energy and nutrient intake will be performed using Foodworks 7 (Xyris Software Pty Ltd., QLD, Australia). Foodworks will be supplemented with food composition data of the pre-packaged foods supplied by the commercial weight-management company for assessment of intervention participants’ week 12 energy and micronutrient intake.

#### Physical activity

In order to monitor physical activity levels, the adolescents in both groups will be required to complete the Adolescent Physical Activity Recall Questionnaire (APARQ), which has been validated in an Australian population [25]; and complete a 4-day activity diary (Children’s Nutrition Centre, University of Queensland, Australia). A pedometer will be worn over the 4- day period and number of steps will be recorded in the activity diary. This will be performed both in the week prior to commencement of the intervention or wait-listed period and repeated at 12 weeks.

#### Participant attitudes to eating, self-image and quality of life

Questionnaires will be completed by both groups both in the week prior to commencement in the study and again at week 12 of the intervention or wait-listed period. The questionnaires will be used to assess the impact of the program on psychosocial factors and also the relationship between baseline psychosocial factors and primary outcomes. General and body specific self-esteem will be assessed via the Rosenberg 5-item self-esteem scale questionnaire [26], and the Mendelson & White 24-item body-esteem questionnaire [27].

The Eating Attitudes Test (EAT)-26 [28] will be used to measure symptoms and concerns characteristic of eating disorders. The items on this scale will be summed to form three subscales; Dieting, Bulimia and Food Preoccupation and Oral Control.

The Strengths and Difficulties Questionnaire (SDQ) adolescent version report will be used to measure adolescent behaviours, emotions and relationships [29]. The items on this scale will be summed to form five subscales; Emotional Symptoms, Conduct Problems, Hyperactivity, Peer Problems, and Pro-social Behaviour.

The Impact of Weight on Quality of Life-KIDS (IWQOL-Kids) will be used to measure obesity specific health related quality of life [30]. The items on this scale will be summed to form four subscales; Physical Comfort, Body Esteem, Social Life, Family Relations.

The 12-item multidimensional perceived social support questionnaire will also be completed to assess three sources of perceived support: family, friends, and significant other [31].

These measures have been validated for use with children and adolescents [26–28, 30, 32–34].

#### Parental involvement

Parents and guardians will be required to complete the Strengths and Difficulties Questionnaire (SDQ) parent version report, a measure of adolescent behaviours, emotions and relationships (Subscales; Emotional Symptoms, Conduct Problems, Hyperactivity, Peer Problems, and Prosocial Behaviour) [29] and a demographic questionnaire prior to their adolescent’s commencement in the study and the SDQ will be repeated during week 12 of the intervention or wait-listed period.

#### Metabolic markers

Participants from both groups will be able to volunteer for further metabolic testing. A subset of participants will opt-in to provide a fasting blood sample at 0 and 12 weeks for the assessment of metabolic markers. Blood will be collected in EDTA containing blood tubes (McFarlane Medical & Scientific, NSW, Australia) and immediately centrifuged at 2000 x g for 15 min at 4 °C. Samples will be stored at-80 °C until analysis.

Glucose, cholesterol and triacylglycerol (TAG) concentrations in plasma will be measured on a Roche Cobas Integra 400 plus auto-analyser (Roche, Lavel, Quebec, Canada) by enzymatic colorimetric methods using commercially available kits (CHOL2, TRIGL and Glucose HK Gen 3) as per the manufacturer’s instructions (Roche, Lavel, Quebec, Canada).

Plasma insulin will be determined using the Human Insulin Specific RIA kit HI–14 K (Merck Millipore, Billerica, MA, USA) according to manufacturer’s instructions and read on a Gamma Counter.

#### Body composition using dual energy x-ray absorptiometry (DXA)

Participants from both groups will be able to volunteer for further body composition assessment. A subset of individuals will opt-in to participate in a whole body DXA scan for body composition at 0, 12 and 36 weeks (intervention only). Participants will attend the laboratory and have their height and weight measured, using standard operating procedures, to determine the correct amount of radiation required for the whole body scan. Whole body composition will be estimated with a GE LUNAR iDEXA Narrow-Angle Dual Energy X-Ray Densitometer with SmartFAN™ (GE Medical, Software Lunar DPX enCORE 2012 version 14.0, Madison, WI).

### Follow-up

All outcome measures will be assessed in the intervention participants at a follow-up at 36 weeks after commencement in the program (6 months after program completion), in order to track longer-term weight management. It will not be possible to follow-up the wait-listed participants as a control group as they will have the option to commence the program at end of their 12-week wait-listed period.

### Statistical analysis plan

Summary descriptive statistics for demographic and clinical data at baseline will be reported by allocated study treatment. Continuous data will be summarised descriptively using either mean and standard deviation, or median and inter-quartile range, depending on the distribution of the variable of interest. Categorical data will be presented as frequencies and percentages. Comparisons between the treatment groups will be conducted to assess the degree to which comparability of randomisation was achieved.

The primary study outcomes are between-group differences in age and gender adjusted BMI Z-score and waist-to-height ratio at 12 weeks. The mean difference between treatment groups will be calculated using linear regression with treatment group entered as the main effect and covariable adjustment for baseline outcome. The corresponding 95 % Wald confidence interval and p-value will be reported. For secondary outcomes, the effect estimate relating to a variable with a binary outcome will be presented as an odds ratio, which will be calculated using a logistic regression model. The effect estimate relating to a variable with a continuous outcome will be presented as a mean difference, which will be calculated using a linear regression model. The effect estimate relating to a variable with a count outcome will be presented as an incident rate ratio, which will be calculated using a Poisson regression model. For all models considering outcomes measured at 12 weeks, the baseline outcome will be included as a covariable. For all models the corresponding 95 % Wald confidence interval and p-value will be reported.

The initial approach to all analyses will be based on the ‘intention to-treat’ (ITT) principle, where all evaluable data is analysed in the treatment group according to which the participant was allocated. Additionally, because of the potential for differential between-group attrition due to the nature of recruitment, all analyses will be investigated to see whether results are sensitive to possible between-group imbalances in key demographic, social, or clinical characteristics. Characteristics of participants for whom follow-up data is available will be compared between groups, and variables significantly different at P < 0.05 will be identified. Multivariable regression models will be run with treatment group as the main effect and covariables including the value of the outcome at baseline and characteristics identified as differing between treatment groups at follow-up. All sensitivity analyses will be clearly labelled., Statistical significance will be defined as alpha = 0.05. All tests conducted will be two-tailed.

Outcomes measured at six months will be analysed using mixed-effects regression models with a random intercept for each participant. For continuous outcomes Gaussian family and identity link function, for binary outcomes a binomial family and logit link function, and for count outcomes a Poisson family and log link function will be used. All models will include time period (baseline/12 weeks/36 weeks) as a main effect, and other covariables will be included as appropriate.

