## Methods

### Study design and participants

The current study is a multicentre, parallel-group randomised controlled trial. Adolescent boys and girls aged 13 to 17 years who apply to join the commercial weight management program will be screened for eligibility to participate. Individuals who do not meet the health screen requirement, a standard practice for enrolment to Jenny Craig weight management programs, will not be eligible for inclusion in the study. Exclusion criteria of the program include being aged less than 13 years or greater than 17 years; having diagnosed diabetes; being pregnant; having given birth to a child during adolescence; having a medical condition or using medications related to weight co-morbidities (except asthma). Individuals who have a BMI Z-score of ≥ 1.282, indicating that they are above the 85^th^ percentile for BMI for their age and gender, will be invited to participate in the study. Participants will be randomised into either the treatment group or the wait-listed control group. The treatment group will enter the weight management program immediately, and the control group will be wait-listed for 12 weeks. Figure 1 shows the study flow. Behavioural questionnaires and diaries will be completed during the week prior to the first consultation where anthropometric characteristics of participants will be recorded. The same questionnaires and diaries will be repeated during week 12 (the final week of the program for participants in the interventions group), and participants will again have anthropometric characteristics recorded at the end of week 12. Primary outcome measures will include changes in BMI Z-score and waist to height ratio. Secondary outcome measures will include changes in physical activity levels, behaviour and psychosocial wellbeing. Participants will have the option to volunteer to have further cardio-metabolic risk factors and body composition examined. All experimental procedures are being conducted in accordance with the Declaration of Helsinki and were formally approved by the Monash University Human Research Ethics Committee (CF11/3687–2011001940).

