### Sample size calculations

For the purpose of sample size estimation, the primary outcome of this study was difference in BMI Z-score at 12 weeks. Our own pilot data, and data from the largest RCT in obese adolescents yet published (209 children aged 8-16 with BMI > 95^th^ percentile; Savoye 2007) suggest the standard deviation in BMI Z-score in a non-passive weight loss intervention will be approximately 0.27. Assuming a 2-sided 0.05 significance level, a sample size of 52 participants per group would provide 80 % power to detect a clinically important treatment difference of 0.15 BMI Z-score. To account for a 25 % drop-out, we plan to enrol 70 participants in each group.

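### Two unranked primary outcomes are each tested at an unadjusted two-sided 0.05 while the trial is sized on one, so an either-outcome efficacy claim would exceed the stated 5% error

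*Protocol article*

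**What the plan says.** Three places in the protocol article name two primary outcomes without ranking them: the Methods paragraph of the Abstract, Study design and participants ("Primary outcome measures will include changes in BMI Z-score and waist to height ratio") and Statistical analysis plan ("The primary study outcomes are between-group differences in age and gender adjusted BMI Z-score and waist-to-height ratio at 12 weeks"). The last of these gives the primary outcomes a linear regression adjusted for the baseline value, with a 95% confidence interval and a p-value.

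The same section then sets one threshold for everything: "Statistical significance will be defined as alpha = 0.05", followed by "All tests conducted will be two-tailed". The two primaries are given neither an alpha split nor an order.

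Sample size calculations uses one outcome: "For the purpose of sample size estimation, the primary outcome of this study was difference in BMI Z-score at 12 weeks". Its inputs are a two-sided 0.05 level, a standard deviation of about 0.27 and a difference of 0.15, and it concludes that "a sample size of 52 participants per group would provide 80 % power to detect a clinically important treatment difference of 0.15 BMI Z-score". Allowing for 25% drop-out, 70 per group are to be enrolled. No effect size, standard deviation or power is given for waist-to-height ratio.

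**The concern.** The article's 0.05 and 80% describe a trial with one primary outcome, but its analysis section declares two. With two p-values, each judged at 0.05, the meaning of those figures depends on what counts as success:

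- If either outcome suffices, there are two chances of a false positive and the error for the efficacy claim is above 5%.
- If both are needed, error is not inflated, but the 80% was worked out for only one of the two hurdles.

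These are alternatives; at most one applies. The case that matters in practice is a split result, significant on one outcome and not on the other. As the article stands, such a result could be called a success or a failure after the data are seen. The trial's purpose is to find out whether a commercial programme is efficacious, so that choice should be fixed in advance.

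**Working it through.** **1. Reproduce the plan's own figure (BMI Z-score alone).** Inputs from Sample size calculations: difference 0.15, SD 0.27, two-sided 0.05, power 80%, drop-out 25%.

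- Normal approximation: n = 2 × (1.960 + 0.842)² × (0.27/0.15)² = 50.9, so 51 per group.
- Two-sample t-test: n = 51.84, so 52 per group; power at 52 is 80.1%.
- Enrolment: 52/0.75 = 69.3, so 70 per group.

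The stated 52 and 70 are correct for BMI Z-score on its own.

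**2. Either outcome suffices: family-wise error.** Let Z₁ and Z₂ be the two test statistics, standard normal under the null hypotheses, with correlation r. The family-wise error is 1 − P(|Z₁| < 1.96 and |Z₂| < 1.96). Under independence this is 1 − 0.95² = 0.0975. For r > 0 the probability comes from the bivariate normal distribution. The article gives no value for r, so it is varied as an assumption.

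| r (assumed) | P(neither significant) | Family-wise error |
|---|---|---|
| 0 | 0.9025 | 9.75% |
| 0.5 | 0.9093 | 9.1% |
| 0.8 | 0.9219 | 7.8% |
| 0.9 | 0.9296 | 7.0% |

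The error is above 5% at every correlation below 1. Two adiposity measures on the same adolescents are likely to be positively correlated, so the lower rows are more relevant than the first.

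**3. Both outcomes required: joint power.** Joint power cannot exceed the power for BMI Z-score. Beyond that bound, the answer turns on inputs that the article does not give. To show how far they move it, assume that waist-to-height ratio has the same standardised effect as BMI Z-score, with 52 per group and the normal approximation:

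- *No gain from baseline adjustment.* The expected test statistic is 0.15/(0.27 × √(2/52)) = 2.83. Joint power is 65% at r = 0, 70% at r = 0.5 and 74% at r = 0.8.
- *0.27 read as a cross-sectional SD, with an assumed baseline-to-12-week correlation of 0.5 for both outcomes.* The residual SD is 0.27 × √(1 − 0.5²) = 0.234 and the expected statistic is 0.15/(0.234 × √(2/52)) = 3.27. Joint power is 82% at r = 0, 84% at r = 0.5 and 86% at r = 0.8.

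The two readings fall on opposite sides of 80%. The article does not say whether 0.27 is the SD of a change or of a value at one time, so joint power cannot be settled from it.

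**4. Effect of a fixed sequence.** BMI Z-score is tested first at 0.05, and waist-to-height ratio at 0.05 only after success. If the BMI Z-score null is true, a false positive on either outcome requires rejecting it, which has probability at most 5%. If it is false, the only possible false positive is on waist-to-height ratio, again at most 5%. The test of BMI Z-score is unchanged, so step 1 stands: 52 evaluable and 70 enrolled per group.

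**The case against.** **A fuller analysis plan may set the order.** The article is condensed, and a testing hierarchy is often left to the full plan. That absence alone would be no finding. But the article's own analysis section positively names two primaries and applies an unadjusted 0.05. A hierarchy set elsewhere would still have to be reconciled with that text and with a sample size based on one outcome.

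**The sample size section already makes BMI Z-score the lead outcome.** It does so only for the calculation, and none of the three statements of the primary outcomes repeats it. The section points towards the natural fix but does not supply it.

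**The inflation is modest and nothing is hidden.** This stands in part. With strongly correlated outcomes the error is 7% to 8%, not nearly 10%; both outcomes will be reported with intervals; and the article describes its results as initial evidence. It also never says that one significant outcome is enough. These points limit the severity but do not restore the 5%.

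**Stronger readings.** A reader might infer that the trial is underpowered for a claim on both outcomes, or that a Bonferroni split would necessarily cut BMI Z-score power from 80% to 71%. The document does not support either as a firm statement. Both ignore the planned baseline adjustment, and the first also needs a waist-to-height effect that is nowhere given. A reader might also infer that waist is the less reliable endpoint. The Anthropometry section has the same trained staff measure weight, height and waist under standard procedures, and nothing in the article ranks their reliability.

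**Conclusion.** The point holds in limited form. The article sets two unranked primary outcomes against one unadjusted 0.05 and a sample size built on BMI Z-score alone. If either outcome can carry the efficacy claim, the family-wise error is about 7% to 9% for assumed correlations from 0.9 down to 0.5, against the stated 5%; 9.75% is the value under independence. These figures rest on normal test statistics and on a correlation that the article does not state.

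If both outcomes are required, there is no error inflation. What can be said is that the 80% refers to BMI Z-score only; whether joint power reaches 80% cannot be determined. The sample size arithmetic itself is sound. This should be fixed before the data are analysed, but it is a matter of ordering the claims and gives no reason to resize the trial.

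**What to change.** In the Abstract (Methods), Study design and participants, and Statistical analysis plan, state that BMI Z-score at 12 weeks is tested first at two-sided 0.05, and that waist-to-height ratio at 12 weeks is tested at two-sided 0.05 only if BMI Z-score is significant. Waist-to-height ratio can stay as the second primary in a fixed sequence or become the first key secondary; error control is the same. Its estimate and confidence interval should be reported in either case.

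The cost is a sentence in each of the three places and no extra recruitment. If BMI Z-score fails, no confirmatory claim on waist-to-height ratio is possible. The trial is registered, so the registry entry may need updating if the status of waist-to-height ratio changes.

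If the sponsor wants either outcome to be able to carry the claim, a split of 0.025 each would also hold 5%. On the plan's unadjusted inputs that takes 63 evaluable per group by t-test, or 63/0.75 = 84 enrolled. The number could be lower if baseline adjustment reduces the residual SD, but that would have to be justified.

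### Prespecify age and sex in the waist-to-height ratio model: as planned, they enter only if a significance test finds them unbalanced (minor, cheap improvement)

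*Protocol article*

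**What the plan says.** All references are to the protocol article.

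- **Primary outcomes** (Statistical analysis plan): "The primary study outcomes are between-group differences in age and gender adjusted BMI Z-score and waist-to-height ratio at 12 weeks".
- **Primary model** (same section): "linear regression with treatment group entered as the main effect and covariable adjustment for baseline outcome". No age, sex or pubertal term is named.
- **Derivation of BMI Z-score** (Anthropometry): "BMI Z-score will be calculated by the lambda-mu-sigma (LMS) method using Centre for Disease Control reference data", "which takes into account age and gender". No such standardisation is given for waist-to-height ratio.
- **Puberty** (Anthropometry): "Participants will be required to self-assess their pubertal status using the Tanner stages of puberty scale". Tanner stage then appears in no named model.
- **Further adjustment** (Statistical analysis plan): characteristics of those with follow-up data are compared between groups, and those differing at P < 0.05 are carried into labelled sensitivity models, with "covariables including the value of the outcome at baseline and characteristics identified as differing between treatment groups at follow-up".
- **Randomisation** (Recruitment and randomisation): 1:1, stratified by centre only.
- **Attrition**: Sample size calculations allows for 25% drop-out. The Statistical analysis plan foresees that loss may differ between groups. Under Ethics and dissemination, a wait-listed adolescent who starts the program early leaves the study.

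**The concern.** The two primary outcomes are treated differently without the text saying so. BMI Z-score arrives at the model already referenced to age and sex. Waist-to-height ratio is an unstandardised ratio in adolescents of 13 to 17 years, whose height is still changing at rates that depend on age and sex. The wording of the outcome sentence leaves it unclear whether waist-to-height ratio is also meant to be adjusted. If it is, the stated model does not do it.

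The route by which age or sex could enter is also a weak one. A significance test on baseline characteristics selects variables by how unbalanced they happen to be, not by how strongly they predict the outcome. It also makes the content of the adjusted model depend on the data. At stake are a chance shift in the second primary estimate, and some protection where drop-out depends on age or sex.

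**Working it through.** **1. Reproduce the plan's figure.** Inputs from Sample size calculations: difference 0.15, SD 0.27, two-sided 0.05, 80% power. The standardised difference is 0.15/0.27 = 0.556. The two-sample t-test needs 51.84 per group, so 52, with power 80.1%. Dropout: 52/(1 − 0.25) = 69.3, so 70. The stated 52 and 70 are correct.

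**2. What the P < 0.05 rule lets through.** Assume an even sex split and 52 evaluable per arm.
- SD of the difference in sex share = √(2 × 0.25/52) = 0.098.
- Imbalance needed for P < 0.05 ≈ 1.96 × 0.098 = 0.192, or about 19 percentage points. Anything smaller is not adjusted for.
- An imbalance of 10 points or more has probability 2 × [1 − Φ(0.10/0.098)] ≈ 0.31.

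**3. Possible shift in the estimate.** Assume boys and girls differ by 0.25 to 0.5 SD in 12-week change; the document gives no figure. The standard error of the treatment difference is √(2/52) = 0.196 SD.
- 10-point imbalance: 0.10 × 0.25 = 0.025 SD to 0.10 × 0.5 = 0.05 SD, which is 13% to 25% of one standard error.
- 19-point imbalance: 0.19 × 0.25 ≈ 0.05 SD to 0.19 × 0.5 ≈ 0.10 SD, which is about 24% to 49% of one standard error.

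**4. Cost and gain of adding age and sex.** No SD or target difference is given for waist-to-height ratio, so this uses the BMI Z-score figures as a stand-in, with 0.27 taken as the residual SD. Let R² be the share of residual variance that the k added terms explain (assumed range).
- The variance is multiplied by (1 − R²) × [1 + k/(104 − 2 − k − 2)], and k degrees of freedom are lost.
- For k = 2 the second factor is 1 + 2/98 = 1.020.
- For age, sex and Tanner stage as five categories, k = 1 + 1 + 4 = 6, and the factor is 1 + 6/94 = 1.064.

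Power at 52 per group, against 80.1% without the terms:

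| Assumed R² | Age + sex (k = 2) | Age + sex + categorical Tanner (k = 6) |
|---|---|---|
| 0 | 79.3% | 77.6% |
| 0.01 | 79.7% | 78.0% |
| 0.02 | 80.1% | 78.4% |
| 0.05 | 81.3% | 79.7% |
| 0.10 | 83.3% | 81.8% |

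The break-even R² is about 2% for age and sex, and about 6% once categorical Tanner stage is added. The largest loss from adding age and sex is 80.1 − 79.3 = 0.8 points.

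**The case against.** The strongest case against is that nothing here is an error. In a 1:1 randomised trial, regression on treatment and the baseline value gives a valid estimate without age or sex. Baseline waist-to-height ratio probably carries much of the age and sex variation already, and growth over 12 weeks happens in both arms. Chance imbalance is reflected in the confidence interval. The sensitivity models also give these variables a way in. All of this stands, with two limits. Validity by randomisation is assured under complete follow-up, which the plan itself does not expect. And the sensitivity route works only above the threshold in step 2.

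Three stronger readings are tempting, and the document does not support them.

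- **That the text contradicts itself.** A reader might infer that both outcomes are declared adjusted while the model adjusts neither. For BMI Z-score the label is accurate, through the LMS derivation. The phrase can be read as describing BMI Z-score alone, and the Abstract and the Study design section list both outcomes without it. The sentence is ambiguous, not demonstrably false.
- **That precision is being given away for free.** Added covariates have a cost, and below about 2% explained variance the change slightly loses power. For waist-to-height ratio itself no gain can be computed.
- **That Tanner stage should be in the model because it is collected.** It is self-assessed, may be missing, and raises the break-even to about 6% if entered as categories.

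**Conclusion.** A minor point that holds as a cheap improvement. Waist-to-height ratio is the only primary outcome with no age or sex adjustment beyond its own baseline, and the plan would supply one only after a significance test and only as a sensitivity analysis. Prespecifying the two terms removes the effect of chance imbalance on them, helps if drop-out depends on them, and takes them out of data-driven selection.

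The size is small. A sex imbalance just under the threshold would move the estimate by at most about half a standard error, and a 10-point imbalance by a quarter or less, if the sexes differ by 0.25 to 0.5 SD. That range, the even sex split and the R² values are assumptions, and the power figures are borrowed from BMI Z-score. The planned estimate is not biased by omitting these terms under complete follow-up, and the 52 and 70 per group stand.

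**What to change.** - Prespecify the waist-to-height ratio model as the 12-week value on treatment, baseline value, age and sex.
- Do not make adjustment for age and sex depend on a test of group differences. The sensitivity models can still be used for other characteristics.
- Reword the outcome sentence so that adjustment for age and sex is attributed to the LMS derivation for BMI Z-score and to the regression model for waist-to-height ratio.
- Adding Tanner stage is optional. If it is used, state how it is coded and how missing self-assessments are handled.

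The cost is wording, plus about 2 of roughly 100 degrees of freedom. No new data are needed: age and sex are already required to compute BMI Z-score. The downside is a power loss of under 1 point if the two variables explain less than about 2% of residual variance.
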